## Abstract

**Background:**

It is estimated that over 240 million people worldwide have osteoarthritis, which is a major contributor to chronic pain and central changes in pain processing, including endogenous pain modulation. The autonomic nervous system plays a crucial role in the pain regulatory process. One of the main mechanisms of remote ischemic conditioning is neuronal signaling from the preconditioned extremity to the heart. This study aims to analyze the acute effect of remote ischemic conditioning on local pain, conditioned pain modulation, and cardiac autonomic control in women with knee osteoarthritis and to see if there is a correlation between them.

**Methods:**

Women more than 50 years with knee osteoarthritis diagnosed according to the American College of Rheumatology criteria in the postmenopausal period will be considered eligible. The study will have blind randomization, be placebo-controlled, and be balanced in a 1:1 ratio. The total of 44 participants will be divided into two groups (22 participants per group): (i) remote ischemic conditioning and (ii) placebo remote ischemic conditioning. Protocol consisting of four cycles of total ischemia, followed immediately by four cycles of 5 min of vascular reperfusion, totaling 40 min. The primary outcomes in the protocol are conditioned pain modulation, which has the pressure pain threshold (kgf/cm^2^) as its primary outcome measure, and cardiac autonomic modulation, which has the indices found in heart rate variability as its primary outcome measure. Comparisons will be performed using generalized linear mixed models fitted to the data. For correlation, the Pearson or Spearman test will be used depending on the normality of the data. All analyses will assume a significance level of *p* < 0.05.

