### Outcomes

#### Conditioned pain modulation

CPM is a dynamic measure capable of evaluating endogenous pain inhibition using a “pain-by-pain inhibition” model in which pain in a local area (test stimulus) is inhibited by a second concomitant pain (conditioning stimulus) [3, 52]. In this study, the test stimulus will be performed through the pressure pain threshold using the algometer, and the conditioning stimulus will be performed through the immersion of the hand in cold water, using the cold pressor test (CPT).

First, the markings of the places where the test stimuli will be performed on the participant will be carried out. The participant will be in dorsal decubitus with approximately 20° of hip and knee flexion with the lower limb comfortably supported and markings will be performed in eight locations on both knees: site 1: 2 cm distal to the lower medial border of the patella; site 2: 2 cm distal to the lower lateral border of the patella; site 3: 3 cm lateral to the midpoint on the lateral edge of the patella; site 4: 2 cm proximal to the upper lateral border of the patella; site 5: 2 cm proximal to the upper edge of the patella; site 6: 2 cm proximal to the upper medial border of the patella; site 7: 3 cm medial to the midpoint on the medial border of the patella; site 8: in the center of the patella [53, 54] and in the joint space between the first and second metacarpophalangeal joints (thenar eminence region of the hand) on the contralateral side [33].

These marked sites will receive the test stimulus through the pressure pain threshold test using a pressure algometer which is a reliable and validated instrument (FDX 50/220; Wagner instruments, Greenwich, Connecticut, USA) which has a tip of 1 cm^2^ [55].

The evaluator will apply pressure perpendicularly to the participant’s skin until she reports the change from pressure sensation to painful sensation [33]. The procedure will be performed three times at each site and the mean values in kgf/cm^2^ will be calculated to determine the pressure pain threshold. An interval of 20 s will be maintained between applications to avoid sensitization of pain responses [33].

After each measurement of the pressure pain threshold, pain will be asked using a visual analog scale (VAS) that ranges from 0 (no pain) to 100 (worst imaginable pain). VAS will also be used to measure knee pain at rest and during CPT [5, 33, 54].

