#### Cardiac autonomic modulation

The collection of data will be carried out individually and the participants will be instructed to remain silent, awake, at rest, and in the supine position. The movement of people on site will be restricted, in order to reduce interference during collection. Participants will be instructed not to consume ANS stimulant substances such as alcoholic beverages, coffee, tea, soft drinks, and chocolate drinks during the 24 h prior to capturing the RR intervals.

The assessment of cardiac autonomic modulation will be performed through HRV by capturing the RR intervals using the heart rate monitor (Polar Electro Oy, Kempele, Finland – model V800) which is a validated equipment [57].

Indices obtained through linear methods, in the time domain (Mean RR, SDNN, and rMSSD), frequency (LF and HF), and the Poincaré plot (SD1 and SD2) will be analyzed [58, 59]. In addition, RR intervals will be analyzed to obtain the 30s rMSSD that represents vagal reentry. All HRV indices will be obtained using the software Kubios HRV – version 3.2 (The Biomedical Signal Analysis Group, Department of Applied Physics, University of Kuopio, Finland) [60].

For this analysis, the time series of RR intervals will be initially submitted to a digital filtering moderated by the software Kubios HRV – version 3.2 [60] complemented by manual filtering, to eliminate premature ectopic beats and artifacts, and only series with more than 95% of sinus beats will be included in the study [58]. Through the visual analysis of the time series, the absence of artifacts or ectopic beats that may interfere with the HRV analysis will be observed.

The series of RR intervals will be analyzed in two different moments: (i) during the performance of the CPM tests and (ii) during the evaluation of the RIC. In order to obtain these analyses, on the first day of the intervention, the following moments will be analyzed: M1 (10 min basal at rest before TOP), M2 (test stimuli through the algometer), M3 (conditioning stimulus, through the CPT), M4 (test stimuli through the algometer), M5 (during RIC), M6 (test stimuli through the algometer), M7 (conditioning stimulus, through the CPT), M8 (test stimuli through the algometer). In these stretches, 256 consecutive RR intervals [59] will be obtained. It is worth noting that at moments M3 and M7, only vagal reentry with a rMSSD of 30 s will be analyzed due to the short time to capture the RR intervals.

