##### Frequency domain

In the frequency domain, the following will be used: the low-frequency spectral component (LF — frequency between 0.04 and 0.15 Hz) index that evaluates the sympathetic and parasympathetic behavior, with sympathetic predominance and the high-frequency component (HF — frequency between 0.15 and 0.4 Hz), which is related as a marker of vagal modulation, in normalized units (nu) and in milliseconds squared (ms^2^) [58, 59]. The spectral indices will be calculated from a tachogram using the fast Fourier transform (FFT) algorithm [58, 59].

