### Statistical analysis

Statistical analysis will be conducted using SPSS software (version 18; SPSS Inc. Chicago, IL, USA). Data normality will be verified by the Kolmogorov–Smirnov test, if normality is detected, the sample characterization variables will be presented as mean and standard deviation/ if not, in median and interquartile range. To compare the characterization of the sample, Student’s *t* test will be used for independent samples.

Descriptive data of outcomes will be presented in mean, standard deviation, and confidence interval values. Comparisons of outcomes between the groups studied and the moments will be performed using Generalized Linear Mixed Models adjusted to the data with Bonferroni post-test when the main analyzes are significant. In addition, the effects of the groups studied will be verified for all outcomes evaluated by calculating the effect size (ES) through Cohen’s *d*, which will be considered as “null” (< 0.2), “small” (≥ 0.2), “moderate” (≥ 0.6), “large” (≥ 1.2) or “very large” (≥ 2.0) [67]. Intention to treat will be used and, for data imputation, a mixed linear model will be used.

To correlate CPM and cardiac autonomic modulation, the Pearson or Spearman correlation test will be used according to the normality of the data. According to the parameters of Portney and Watkins [68], the correlation magnitude of 0.00 to 0.19 is considered to be very weak; 0.20 to 0.39 weak correlation; 0.40 to 0.69 moderate correlation; 0.70 to 0.89 strong correlation and 0.90 to 1.00 very strong correlation [68]. All analyses will assume a significance level of *p* < 0.05.

The external evaluator will enter the data into the database for screening, randomization, and statistical analysis. Dual data entry in electronic format will be used. Data integrity will be monitored regularly by examining data files for omissions and errors. Participants will receive an anonymous study ID to protect confidentiality, and only study investigators will have access to the final study dataset. The spreadsheets containing the raw numerical data of the data generated in this study will be stored in their entirety initially on two external hard drives and two online clouds. Any data needed to support the protocol can be provided upon request.

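### One of the two primary outcomes is an unranked set of 8 to 10 HRV variables, and no alpha rule covers the set or the two primaries together

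*Protocol article*

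**What the plan says.** **Primary outcomes (Abstract, Methods).** "The primary outcomes in the protocol are conditioned pain modulation, which has the pressure pain threshold" in kgf/cm² as its measure; the other is "cardiac autonomic modulation, which has the indices found in heart rate variability as its primary outcome measure".

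**HRV variables (Cardiac autonomic modulation; Frequency domain).** Indices "in the time domain (Mean RR, SDNN, and rMSSD), frequency (LF and HF), and the Poincaré plot (SD1 and SD2) will be analyzed". In addition, "RR intervals will be analyzed to obtain the 30s rMSSD that represents vagal reentry". LF and HF are each reported "in normalized units (nu) and in milliseconds squared". Eight moments are analysed on day 1 and three on day 2. At M3 and M7 only the 30-s rMSSD is used.

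**CPM (Conditioned pain modulation).** For the pressure pain threshold, "markings will be performed in eight locations on both knees", plus one site on the hand. CPM is computed as a difference in threshold, and a percentage change is calculated as well. The section does not say which site or average is decisive.

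**Error rule (Statistical analysis).** "All analyses will assume a significance level of" p < 0.05. Outcomes are compared with generalized linear mixed models, followed by Bonferroni post-tests when the main analysis is significant.

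**Status of the trial.** Trial design calls it exploratory. The Introduction announces two hypotheses to be tested and puts local pain, CPM and cardiac autonomic control in the primary objective. Sample size is based on CPM alone: two-tailed, 5% level, 80% power, 19 per group raised to 22.

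**The concern.** A primary outcome should tell the reader in advance which result answers the question. Here the HRV primary is a family with no leading member and no stated contrast. Each member is tested at the full 5%, and so is CPM. The Bonferroni post-test works among moments and groups inside one model. It does not act between rMSSD and SDNN, or between HRV and CPM. Nor does the article say whether one positive primary suffices or both are needed.

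The risk is that an effect on cardiac autonomic modulation is reported as a primary finding because one of several indices crossed 0.05. One index is also close to a copy of another. SD1 is the standard deviation of successive RR differences divided by √2, so with a mean difference near zero it equals rMSSD/√2. A chance result in rMSSD would then appear twice and look like corroboration.

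Local pain raises a smaller, related mismatch: it is in the primary objective but not among the primary outcomes.

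**Working it through.** **1. The plan's own figure.** Sample size gives 98 ± 103 kPa. Read as a difference and a standard deviation, d = 98/103 = 0.951. For a two-sided t-test with n per group, the noncentrality is d·√(n/2) on 2n − 2 degrees of freedom. At α = 0.05 the power is 79.2% at n = 18 and 81.4% at n = 19. The stated 19 per group is reproduced, as the size for one CPM test. No power is given for any HRV index.

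**2. Counting the HRV primary.** Mean RR, SDNN, rMSSD, LF, HF, SD1 and SD2 make 7; the 30-s rMSSD makes 8. A second unit for each of LF and HF makes 10 variables.

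**3. False-positive risk if tests are independent.** One group comparison per variable, 1 − 0.95^k:
- one CPM and one HRV test, k = 2: 9.8%
- 8 HRV + 1 pooled CPM, k = 9: 37.0%
- 10 HRV + 1 pooled CPM, k = 11: 43.1%

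Leaving out SD1 as a duplicate gives k = 8, 33.7%, and k = 10, 40.1%.

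**4. With correlated indices.** The article gives no correlations, so these are assumed. The table is from simulated two-group t-tests: 19 per group, 8,000 runs, equal correlation ρ among the HRV variables (and among CPM sites in the last column), HRV independent of CPM.

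| ρ | 8 HRV + 1 CPM | 10 HRV + 1 CPM | 10 HRV + 17 CPM sites |
|---|---|---|---|
| 0 | 37% | 44% | 75% |
| 0.3 | 33% | 38% | 69% |
| 0.5 | 29% | 33% | 57% |
| 0.7 | 24% | 26% | 44% |
| 0.8 | 21% | 22% | 35% |
| 0.9 | 17% | 17% | 26% |

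The last column takes 8 sites × 2 knees + 1 hand site = 17, each tested separately. The text permits this but does not state it, so it is an upper case for one CPM metric.

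**5. Moments are not added to the count.** M1–M4 and Pre-RIC precede the intervention, so they give no treatment-effect test. M3 and M7 carry a single index. Within a model, the post-test gives some control across moments.

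**6. Cost of each alpha rule for CPM, at d = 0.951.**
- Fixed sequence with CPM first: α = 0.05, power 81.4% at 19 per group, no change.
- Split, 0.025 each: power 72.2% at 19 and 79.4% at 22; 23 evaluable per group are needed for 80%.
- Bonferroni over all 11 variables (10 + 1): power 47.3% at 19; 32 per group are needed. Adjusting for the whole set is therefore not a practical substitute for choosing.

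**The case against.** **The trial is called exploratory.** This is the best counter-argument, and part of it stands: an exploratory trial need not control error across everything it measures. But the same article names primary outcomes, announces hypotheses to be tested and justifies its size by a two-tailed 5% test. If exploratory is meant, the significance claims should go; if tests are meant, they need a rule.

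**An article may leave detail to an analysis plan.** This stands for how the CPM sites are pooled, and so the main figures count CPM once. It does not cover the HRV primary or the 5% rule, both of which the article states.

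**Stronger readings that the text does not support.**
- A reader might infer that CPM is primary at 17 sites in two metrics. The sites are where thresholds are measured, and no sentence says that each is tested. The Abstract names the threshold in kgf/cm², and the percentage is only an added calculation.
- A reader might infer ten indices tested at eleven moments. Two of those moments carry one index, and several precede the intervention.
- A reader might infer that the first hypothesis could be claimed from any single positive test. It joins the two domains: autonomic improvement and, as a consequence, better CPM. If HRV and CPM are independent, the chance of a false positive in both is 0.401 × 0.05 = 2% with ten independent HRV variables and one pooled CPM value, and 0.401 × 0.582 = 23% with 17 independent sites. The 37% and 43% figures concern any primary result, not that joint claim. The Statistical analysis section does not, however, require both to succeed.

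**Conclusion.** The point holds. The HRV primary is an undesignated set, CPM has no named decisive summary, and no error control spans the indices or the two primaries. The chance of at least one false-positive primary result is about 17% to 37% for eight HRV indices and one pooled CPM value, across assumed correlations from 0.9 to 0, and 43% for ten plus one if independent. It is higher if CPM sites are tested separately, which the article leaves open.

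A reader might go further and call a false-positive primary finding likely. That would need more than 50%, which is reached only when the CPM sites are counted separately and correlation is low to moderate. On the narrower counts the accurate statement is that the risk is several times the nominal 5%.

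The figures assume one group comparison per variable, equal correlation within HRV, and independence between HRV and CPM. Some variables overlap heavily (SD1 with rMSSD, and LF with HF in normalized units), so the effective number of tests is below the raw count. No assumption examined brings the risk near 5%.

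**What to change.** Before recruitment, in the protocol, registry and analysis plan:

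1. Designate one CPM summary: one site or one site average, as the absolute difference.
2. Designate one HRV index at one post-intervention contrast. The choice of index is the sponsor's.
3. State an alpha rule. One option is a fixed sequence, each step at 5%, in an order the sponsor chooses. With CPM first, 19 evaluable per group stays valid; with HRV first, the size needs its own justification. The other option is 2.5% for each primary, with CPM power restated as about 72% at 19 or 79% at 22 per group.
4. Report all other indices, sites and moments, and the percentage metric, as exploratory, with confidence intervals and no significance claims. Do not test SD1 separately from rMSSD.
5. Align objective and outcomes by listing resting knee pain on the VAS, which is already collected, as the local-pain secondary outcome.

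The cost is wording only, since Trial status says that recruitment has not begun. The price is fewer confirmatory HRV claims; under a fixed sequence the second endpoint can be claimed only if the first succeeds.

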**Discussion:**

It is believed that the results of this study will present a new perspective on the interaction between the pain processing system and the cardiovascular system; they will provide the professional and the patient with a greater guarantee of cardiovascular safety in the use of the intervention; it will provide knowledge about acute responses and this will allow future chronic intervention strategies that aim to be used in the clinical environment, inserted in the multimodal approach, for the treatment of osteoarthritis of the knee.

**Trial registration:**

ClinicalTrials.gov NCT05059652. Registered on 30 August 2021. Last update on 28 March 2023.

**Supplementary Information:**

The online version contains supplementary material available at 10.1186/s13063-023-07527-2.

## Introduction

Early prevention and treatment of musculoskeletal disorders and targeting risk factors for associated chronic diseases can play an important role [1]. However, a greater understanding of why musculoskeletal conditions increase the risk of chronic disease is needed. As in the case of osteoarthritis, which appears to increase the risk of developing cardiovascular disease [1].

It is estimated that more than 240 million people worldwide have symptomatic osteoarthritis and among the risk factors for knee osteoarthritis are advanced age and female sex [2]. In addition, individuals with osteoarthritis have lower levels of physical activity [2], which is a major contributor to chronic pain and central changes in pain processing [3].

The pain processing system includes endogenous pain modulation, characterized by the ability of the central nervous system (CNS) to modulate nociceptive input from peripheral tissues as it ascends to the spinal cord, brainstem, and brain [4]. This modulation can lead to an increase or inhibition of pain perception. Furthermore, a dysfunctional modulation may be part of the pathophysiology of chronic pain [4].

Endogenous pain modulation can be investigated through the conditioned pain modulation (CPM) test, which is characterized by the reduction of pain perception caused by intense pain in a remote area of the body and represents the outcome of descending pain inhibitory mechanisms [5, 6]. In summary, among the functional impairments [1] and CNS mechanisms [2] presented by patients with osteoarthritis, the presence of pain due to less efficient endogenous inhibition can be highlighted.

Furthermore, the autonomic nervous system (ANS) plays a crucial role in modulating perception, functional interaction, and pain regulation [7, 8]. The interaction between ANS and pain perception has been shown to be an important contributor to the pain regulatory process [9, 10]. Heart rate variability (HRV) is a reliable non-invasive way to assess ANS modulation. Several chronic pain conditions are being associated with alterations in the ANS function, assessed through HRV indices [11–14].

In summary, the systems involved in autonomic control are strictly linked to those involved in pain perception, and, therefore, HRV can be considered an index of ANS reactivity to nociceptive stimulation [15]. Patients with chronic pain, such as osteoarthritis, have reduced HRV and baroreflex sensitivity due to changes in efferent sympathetic and parasympathetic cardiac activity, which alter the balance to a prevalence of sympathetic tone related to catecholamine release [16, 17].

HRV is also related to the endogenous modulation of pain, a relevant factor in the development and maintenance of pain [18]. Furthermore, endogenous pain modulation and HRV are linked in both the presence and absence of chronic pain. Thus, HRV has several advantages in studies that investigate the physiological response to nociceptive stimulation [19–21].

According to a recent systematic review by Forte et al. [22], as HRV appears to be impaired in several chronic pain conditions that can worsen the quality of life, future researchers and clinicians may benefit from using HRV to assess the effectiveness of treatments in pain management in clinical populations [22].

Therefore, the effect of chronic pain presented by individuals who have osteoarthritis may provide adaptation in the autonomic regulation of the cardiovascular system. Taking this into account, treatment approaches that generate changes in pain processing behavior and cardiac autonomic modulation need to be further explored.

An approach that has been used to improve muscle performance and that is widely used in the management of cardiovascular disorders because it is considered an intrinsic mechanism that has the ability to protect tissues against the deleterious effects of ischemia–reperfusion is remote ischemic conditioning (RIC) [23]; however, little is known about the effect of this intervention for pain management [24] and its repercussion on the CPM and cardiac autonomic control systems. There is no evidence that RIC causes systemic hypoalgesia, so these gaps provide a rationale for future research.

The RIC is characterized by the application of brief periods of circulatory occlusion (ischemia) and reperfusion of a limb through inflation and deflation of a pressure cuff [25]. Thielmann et al. [26] demonstrated reduced myocardial damage from RIC, including improvement in clinical outcomes in patients undergoing cardiac surgery and in those with myocardial infarction undergoing emergency coronary artery stent implantation [26].

One of the main mechanisms of RIC appears to be neuronal signaling from the preconditioned extremity to the heart [27]. Current data reveal that there are interactions of neuronal and humoral pathways and activation of peripheral sensory nerves, resulting in a release of cardioprotective factors that circulate to target organs via the bloodstream [28–30]. In this way, the ANS can be modified using the RIC, which, in turn, can be proven by the HRV indices.

Given the ease of administration of the intervention, in addition to its low cost and not being an invasive method, RIC can be investigated as a possible multimodal analgesic strategy [24]. However, further studies are needed on the impact of different RIC strategies, elucidation of mechanisms, safety profiles, and cost-effectiveness. Furthermore, understanding the immediate cardiovascular benefits of RIC will support the development of strategies in the primary and secondary prevention of cardiovascular disease [27].

Taking into account that the RIC can result in an improvement in cardiac autonomic modulation through the activation of neuronal pathways and that this activation can reflect in a better management of the patient’s pain, the following gaps were raised: Is the RIC capable of improving local pain after its application in women with osteoarthritis? Does RIC cause changes in CPM systems and cardiac autonomic modulation? Is there a correlation between CPM and cardiac autonomic modulation?

From these gaps, two hypotheses will be tested. First, that RIC is able to improve cardiac autonomic modulation and consequently improve CPM in women with knee osteoarthritis. Second, that there is a correlation between CPM and cardiac autonomic modulation in women with knee osteoarthritis. Therefore, the primary objective of the study will be to analyze the acute effect of RIC on local pain, CPM, and cardiac autonomic control systems in women with knee osteoarthritis. The secondary objective will be to observe if there is a correlation between CPM and cardiac autonomic modulation in women with knee osteoarthritis.

Information of this nature is important to guide therapists on aspects of intervention related to CPM and cardiac autonomic modulation, about reducing pain and improving autonomic control, and in this way, it provides guiding knowledge for future long-term studies on other chronic diseases and cardiovascular events.

